### Study endpoints

Primary endpoint: post-operative complications in first 90 days following IORT will be recorded as a binary variable (≥ Clavien-Dindo grade IIIa or < Clavien-Dindo grade IIIa). Clavien-Dindo classification is displayed in Table 2 [23].

**Table 2 Tab2:** Clavien-Dindo classification

Grade I	Any deviation from the normal postoperative course without the need for pharmacological treatment or surgical, endoscopic, and radiological interventions. Allowed therapeutic regimens are: drugs as antiemetics, antipyretics, analgesics, diuretics, electrolytes, and physiotherapy. This grade also includes wound infections opened at the bedside
Grade II	Requiring pharmacological treatment with drugs other than such allowed for grade I complications Blood transfusions and total parenteral nutrition are also included
Grade III	Requiring surgical, endoscopic or radiological intervention
IIIa	Intervention not under general anesthesia
IIIb	Intervention under general anesthesia
Grade IV	Life-threatening complication (including CNS complications)* requiring IC/ICU management
IVa	Single organ dysfunction (including dialysis)
IVb	Multi-organ dysfunction
Grade V	Death of a patient

^*^Brain hemorrhage, ischemic stroke, subarachnoid bleeding, but excluding transient ischemic attacks

*CNS* Central nervous system, *IC* Intermediate care, *ICU* Intensive care unit

Secondary endpoints are as follows: 1. Post-operative complications after 90 days following IORT will be recorded as a binary variable (≥ Clavien-Dindo grade IIIa or < Clavien-Dindo grade IIIa), 2.Local progression-free will be recorded as time from IORT to first occurrence of locoregional or last known negative imaging. Locoregional failure will include disease recurrence occurring within the surgical bed, extra-pancreatic perineural tracts, regional nodal basins, or the triangle volume, 3. Overall survival will be recorded as the time from IORT to death or last known clinic follow-up, 4. Distant metastasis-free survival will be measured from time of IORT to the development of distant progression or last known negative imaging. 5. Progression-free survival will be measured as the interval from the end of IORT to the time of the first radiographic evidence of any failure, death, or last known negative imaging.

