**Methods:**

Patients with non-metastatic pancreatic adenocarcinoma centered in the head or neck of the pancreas will be enrolled. Following treatment with multi-agent neoadjuvant chemotherapy, patients will undergo SBRT (40 Gy/5 fractions) followed by IORT (15 Gy/1 fraction) to the TV during the Whipple procedure. The primary objective is acute (< 90 days) toxicity after IORT measured by Clavien-Dindo classification. Secondary objectives include late (> 90 days) toxicity after IORT measured by Clavien-Dindo classification, overall survival, local progression-free survival, distant metastasis-free survival, and progression-free survival.

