## Background

Pancreatic adenocarcinoma (PDAC) is the third most common cause of cancer related deaths in the United States, responsible for over 48,000 deaths each year [1]. At time of diagnosis, approximately 10% are resectable, 40% are borderline resectable (BRPC) or locally advanced (LAPC), and the remaining 50% are metastatic. Treatment of localized disease usually involves a combination of multi-agent chemotherapy, radiation therapy, and surgery [2]. Unfortunately, even with aggressive therapy, prognosis is poor with 5-year overall survival (OS) of less than 15% [3].

Improvements in chemotherapy and radiation therapy have increased the proportion of patients with non-metastatic disease who can undergo surgery [4, 5]. However, after surgery, while distant failure predominates, a not insignificant portion of patients (30–40%) develop local recurrence [6, 7]. In fact, one report demonstrated that 30% of all pancreatic cancer patients die from locally destructive disease [8]. This suggests that there may be a role for intensification of local therapies such as radiation. However, dose escalation of radiation therapy in this context is limited by proximity to gastrointestinal structures and in particularly the duodenum. Given that the duodenum is resected during Whipple surgery, intra-operative radiation therapy (IORT) provides a unique opportunity to intensify radiation delivery for pancreatic cancer and further escalate the radiation dose delivered beyond what is feasible with external beam radiation therapy alone, even with modern technologies such as stereotactic body radiation therapy (SBRT). Additionally, IORT allows for shielding of other normal organs, direct visualization of the target, and elimination of positional uncertainties.

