## Methods/design

### Objectives

The primary objective is to evaluate acute post-operative toxicity (< 90 days) of IORT targeted to the TV in patients with non-metastatic pancreatic adenocarcinoma undergoing surgical resection after neoadjuvant multi-agent chemotherapy and SBRT.

The secondary objectives are as follows: 1.To evaluate late toxicity (> 90 days) of IORT targeted to the TV in patients with non-metastatic PDAC undergoing surgical resection after neoadjuvant multi-agent chemotherapy and SBRT, 2. Estimate median local progression-free survival (LPFS) from time of IORT, 3. Estimate median overall survival (OS) from time of IORT, 4. Estimate median distant metastasis-free survival (DMFS) from time of IORT and 5. Estimate median progression-free survival (PFS) from time of IORT.

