#### Follow-up

Patients will follow-up in clinic every 3 months with imaging for the first 2 years post-surgery and then every 6 months with imaging for years 3–5 post-surgery. During each follow-up visit, patients will undergo a physical exam, assessment of performance status, and have routine blood work including cancer antigen 19–9. Additionally, chemotherapy-induced and radiation-induced toxicity will be assessed using the Common Terminology Criteria for Adverse Events (CTCAE) criteria (v5.0). Surgical- toxicity will be assessed using Clavien-Dindo classification. Toxicity will be evaluated at each follow-up visit. Disease progression and response will be assessed using Response Evaluation Criteria in Solid Tumors (RECIST) criteria (v1.1).

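### Late toxicity of IORT is defined only on the surgical complication scale, and the CTCAE radiation toxicity collected at every visit enters no stated endpoint

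*Protocol article*

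**What the plan says.** The Objectives section lists as first secondary objective: "To evaluate late toxicity (> 90 days) of IORT targeted to the TV in patients with non-metastatic PDAC undergoing surgical resection". The Methods part of the abstract names the scale: "late (> 90 days) toxicity after IORT measured by Clavien-Dindo classification". The Study endpoints section makes this operational: "Post-operative complications after 90 days following IORT will be recorded as a binary variable", with grade IIIa or higher against anything lower.

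The Follow-up section divides the two scales by cause of harm. For drug and radiation effects, "chemotherapy-induced and radiation-induced toxicity will be assessed using the Common Terminology Criteria for Adverse Events (CTCAE) criteria (v5.0"). For surgical effects, "toxicity will be assessed using Clavien-Dindo classification". It adds: "Toxicity will be evaluated at each follow-up visit". Footnote 1 of Table 1 lists both scales for the toxicity assessment.

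Table 2 places complications treated with drugs beyond the basic ones, with transfusion or with parenteral nutrition in grade II. Procedures are grade III, life-threatening events needing intermediate or intensive care are grade IV, and grade V is "Death of a patient".

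**The concern.** IORT is radiation, and its late effects are the subject of the objective. The endpoint that serves this objective uses the scale that the same article assigns to surgery, while the scale it assigns to radiation is collected and then left out of every stated endpoint. Clavien-Dindo grades a complication by how it was treated. After day 90, how a harm is treated and whether radiation caused it are separate questions, so the binary can miss radiation harm and can also count events that radiation did not cause.

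The stopping rule ends at day 90. Beyond that point this binary is the only late-safety measure that the article commits to, for a regimen whose stated novelty is a combined BED10 of 109.5 Gy to the triangle volume.

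**Working it through.** The article states no rate, precision or power for late toxicity, so there is no figure to reproduce. The check compares the sections and then illustrates the size under assumptions.

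**Step 1. Which scale feeds which measure.**

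| Measure | Scale or data used |
|---|---|
| Primary endpoint (first 90 days) | Clavien-Dindo IIIa or higher |
| Secondary endpoint 1 (after 90 days) | Clavien-Dindo IIIa or higher |
| Secondary endpoints 2 to 5 | Time to progression or death |
| Stopping rule (through day 90) | Rate set from 90-day Clavien-Dindo IIIa or higher |
| Radiation toxicity at each visit | CTCAE v5.0; feeds none of the rows above |

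The Statistical analysis section does not mention a CTCAE summary either.

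**Step 2. What the binary can miss.** By Table 2, late harm treated with drugs, transfusion or parenteral nutrition is grade II or lower, so it is recorded as no event. Late harm that needs a procedure or intensive care is grade IIIa or higher and is still counted. The loss is therefore partial.

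Illustration (assumed rates; the document gives none): let L be the true proportion with clinically relevant late radiation harm, and s the share of that harm managed at grade II or below. Then

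counted proportion = L × (1 − s), and expected count = 20 × L × (1 − s),

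where 20 is the number expected to receive IORT (Statistical analysis and sample size).

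| L (patients of 20) | s = 20% | s = 40% | s = 60% |
|---|---|---|---|
| 10% (2) | 8% (1.6) | 6% (1.2) | 4% (0.8) |
| 20% (4) | 16% (3.2) | 12% (2.4) | 8% (1.6) |
| 30% (6) | 24% (4.8) | 18% (3.6) | 12% (2.4) |

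The article does not reproduce the CTCAE grades. L therefore stands for relevant harm in general, not for a particular CTCAE grade.

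**Step 3. What the binary can add.** No attribution to IORT, SBRT or tumour is stated for events after day 90, and follow-up runs to year 5. The Background puts local recurrence after surgery at 30–40%, which for 20 patients is 0.30 × 20 = 6 to 0.40 × 20 = 8. Not all of these would need a procedure, but any procedure for recurrence meets the wording of grade III.

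**Step 4. Deaths and unequal follow-up.** The Background cites a comparison of resected patients with median survival of 35.1 months with IORT and 24.5 months without. Assuming exponential survival from a comparable starting point:

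- Deaths by 2 years: 1 − 0.5^(24/35.1) = 38% and 1 − 0.5^(24/24.5) = 49%, or about 8 to 10 of 20.
- Deaths by 5 years: 1 − 0.5^(60/35.1) = 69% and 1 − 0.5^(60/24.5) = 82%.

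Time at risk for late harm will therefore differ greatly between patients. In a plain proportion, a patient who dies of cancer early without a recorded complication would weigh the same as one followed for 5 years.

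Steps 2 and 3 push the rate in opposite directions. The net bias is not known, and a rate close to the truth could arise by cancellation.

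**The case against.** Four objections deserve weight.

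- **The endpoint is confined to post-operative complications.** A reader might take grade V literally, pair it with the Background's "prognosis is poor with 5-year overall survival (OS) of less than 15" per cent, and infer that at least 1 − 0.15 = 85% of patients would score as late toxicity. The documents do not support that. Counting a cancer death in a later year drops the noun that defines the endpoint. The survival figure describes localized disease in general, not patients who were free of metastases after chemotherapy and then resected. Deaths before day 90 also belong to the primary endpoint. What remains is that the article does not say which late deaths or procedures count. Nor can the same death both count as grade V and be scored as free of toxicity; these are alternative readings, and the text does not choose between them.
- **Estimator, censoring and attribution are usual analysis-plan content.** This stands: their absence is not the finding. The scale, the cut-point and the binary form are fixed in the article itself, and they conflict with its own division of the scales.
- **CTCAE data are collected and can be reported.** True, and it makes the repair cheap. But no stated endpoint commits to using them.
- **Late toxicity is secondary.** A reader might infer that the trial cannot support any safety conclusion. That goes too far, because the main safety judgement rests on the 90-day endpoint and its stopping rule, which this point leaves untouched.

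Comparability with past data is a reason to keep Clavien-Dindo, but the only historical rate given, 25%, is a 90-day rate. It does not require Clavien-Dindo as the sole late measure.

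**Conclusion.** The point holds as a mismatch within the document. Late toxicity of a radiation treatment is measured only on the scale that the Follow-up section assigns to surgery, and the radiation scale feeds no stated endpoint. The consequence is partial misclassification in both directions: medically managed radiation harm goes uncounted, and recurrence-related procedures or deaths may be counted. It would be wrong to say that all late radiation harm is misclassified.

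The size cannot be fixed from the document. Under the assumed inputs, a true 20% would be seen as 16% down to 8% before any wrongly added events. This should be corrected because it bears on the late-safety evidence before a phase II trial. It does not undermine the primary endpoint.

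**What to change.** In the Study endpoints section and in the abstract, define the late-toxicity endpoint as CTCAE v5.0 grade 3 or higher toxicity attributed to SBRT/IORT, with onset after day 90. Joint attribution is practical because both treatments cover the triangle volume. Keep late Clavien-Dindo grade IIIa or higher as a descriptive measure, excluding events due to tumour progression.

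Because follow-up will differ between patients and deaths are expected, the CTCAE endpoint is preferably reported as cumulative incidence with death as a competing event rather than as a plain proportion.

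The cost is a wording change and an attribution entry for each event, which brings some judgement into the endpoint. No new visits or tests are needed, since both scales are already assessed at each follow-up visit.

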### Statistical analysis and sample size

Descriptive statistics will be utilized to record patient demographic, disease, and treatment characteristics including age, sex, race, disease extent, chemotherapy, radiation therapy, and type of surgery. Time to event outcomes such as OS, LPFS, DMFS, and PFS will be analyzed using Kaplan–Meier method. Our institution’s data and experience suggest that 15% of patients will not be surgically explored due to development of radiographic metastatic disease or too locally extensive disease after SBRT. An additional 15% will require unexpected arterial reconstruction (exclusion criteria). Therefore, 25 patients will be enrolled with the expectation that 20/25 patients will undergo surgical exploration and IORT. A sample size of 20 patients was chosen because this will enable safety evaluation using a closely monitored Bayesian stopping rule and is also recommended by the literature [21, 22]. There will not be any interim data analysis. Data analysis will occur once the study has been completed.

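### LPFS and DMFS are defined without death as an event, which conflicts with their names, with the medians promised in the objectives and with the PFS definition beside them

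*Protocol article*

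**What the plan says.** All statements are in the protocol article.

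- **Objectives.** Two secondary objectives are "Estimate median local progression-free survival (LPFS) from time of IORT" and "Estimate median distant metastasis-free survival (DMFS) from time of IORT". Both are named as survival endpoints, and a median is the target.
- **Study endpoints, LPFS.** "Local progression-free will be recorded as time from IORT to first occurrence of locoregional or last known negative imaging". The sentence that follows says what counts: "Locoregional failure will include disease recurrence occurring within the surgical bed, extra-pancreatic perineural tracts, regional nodal basins, or the triangle volume". Every item is a site of recurrence.
- **Study endpoints, DMFS.** "Distant metastasis-free survival will be measured from time of IORT to the development of distant progression or last known negative imaging".
- **Study endpoints, PFS.** Here the interval runs to the "time of the first radiographic evidence of any failure, death, or last known negative imaging", so death is an event.
- **Study endpoints, OS.** "Overall survival will be recorded as the time from IORT to death or last known clinic follow-up". Deaths are therefore collected.
- **Statistical analysis and sample size.** "Time to event outcomes such as OS, LPFS, DMFS, and PFS will be analyzed using Kaplan–Meier method". No competing-risk method is named.

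**The concern.** An endpoint called local progression-free survival, or distant metastasis-free survival, ends at the named failure or at death. The written rule for both has only the failure as an event, with the last negative scan as the only other end of follow-up. A patient who dies without that failure can then only be censored at that scan. Kaplan–Meier treats censored patients as if they could still fail later at the same rate as those under follow-up, and a dead patient cannot.

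This is not a rare event here. The Background puts 5-year survival of localized disease below 15% and says that distant failure predominates after surgery. Many patients may therefore die without documented local failure.

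What is at stake is how two secondary results are read. A median labelled LPFS would not be the time for which half the patients are alive and free of local progression. A reader who took one minus the curve as the risk of local failure would read it too high.

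**Working it through.** **Definitions side by side**

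| Endpoint | Event | Otherwise ends at | Death an event? |
|---|---|---|---|
| LPFS | locoregional failure | last negative imaging | not listed |
| DMFS | distant progression | last negative imaging | not listed |
| PFS | any failure, death | last negative imaging | yes |
| OS | death | last clinic follow-up | yes |

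The article states no median, event count or power for LPFS or DMFS, so there is no figure of its own to reproduce. What follows only illustrates size, for LPFS.

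**Illustration 1: inputs borrowed from the Background**

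Assumptions:
- Constant hazards: *l* for local failure and *d* for death without local failure.
- Median time to death without local failure, *M* = 24.5 or 35.1 months. In the Background these are overall median survival times from a retrospective comparison of resection without and with IORT. Their use for this hazard is an assumption.
- Observed local failure by 60 months, *c* = 30% or 40%. The Background gives 30–40% with no time point, so the 5-year horizon is an assumption.

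Formulas:
- *d* = ln 2 / *M*
- *l* solves *l*/(*l*+*d*) × (1 − exp(−60(*l*+*d*))) = *c*
- median as written (death censored) = ln 2 / *l*
- median with death counted = ln 2 / (*l*+*d*)
- one minus Kaplan–Meier at 60 months = 1 − exp(−60*l*)

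One case in full, *M* = 24.5 and *c* = 0.40: *d* = 0.6931/24.5 = 0.02829 and *l* = 0.02069. Check: 0.02069/0.04898 = 0.422, and 0.422 × (1 − exp(−2.939)) = 0.422 × 0.947 = 0.40. The medians are 0.6931/0.02069 = 33.5 and 0.6931/0.04898 = 14.2 months.

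| *M* (months) | *c* | Median as written | Median, death counted | Ratio | 1−KM at 60 months |
|---|---|---|---|---|---|
| 24.5 | 30% | 50.6 | 16.5 | 3.1 | 56% |
| 24.5 | 40% | 33.5 | 14.2 | 2.4 | 71% |
| 35.1 | 30% | 63.3 | 22.6 | 2.8 | 48% |
| 35.1 | 40% | 42.6 | 19.2 | 2.2 | 62% |

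The last column is to be compared with *c*, the cumulative incidence that was put in.

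**Illustration 2: different assumptions**

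Here the median of the composite (local failure or death) is assumed to be *m* = 12, 18 or 24 months, and a share *p* = 0.30 or 0.40 of first events is assumed to be local. The local hazard is then *p* × ln 2 / *m*, so the death-censored median is *m*/*p*.

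- *p* = 0.40: 30, 45 and 60 months.
- *p* = 0.30: 40, 60 and 80 months.

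The inflation is 1/*p*, that is 2.5- to 3.3-fold. One minus Kaplan–Meier at 60 months runs from 0.41 to 0.75 across the six cases, against a cumulative incidence of 0.25 to 0.39.

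These six cases were also simulated with 20 patients, the article's imaging schedule (every 3 months in years 1–2, every 6 months in years 3–5) and 3,000 trials each. The as-written median was at or above the death-counted median in every trial. It was not reached by 60 months in 11% to 70% of trials, depending on the case. The death-counted median was reached in effectively all of them.

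**DMFS** has the same structure. Its size is not computed, because the article gives no share for distant failure.

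**The case against.** - **Censoring at death is inferred.** The article nowhere says in words that deaths are censored. The LPFS sentence is visibly incomplete, and the word survival in the Objectives suggests that death may have been intended, so careless condensation is plausible. This stands as a caution on intent. It does not remove the conflict, because the definitions are given, not left to another document, and PFS in the same list names death.
- **Time to failure may have been intended.** Censoring deaths then estimates a cause-specific quantity, and the medians are not inflated against that target. This also stands, but then the names are wrong and the curve cannot be read as a failure risk. Neither reading makes the three sections agree.
- **The figures rest on borrowed inputs.** Overall survival includes deaths after local failure, so using it for death without local failure overstates that hazard. The 5-year horizon for local failure is added. A reader might infer that the protocol's own data show a roughly threefold inflation. They do not; the two illustrations agree on direction but not on size.
- **Little depends on these endpoints.** A reader might infer that the trial's conclusions or the step to phase II are compromised. The Abstract, Background and Discussion tie that step to safety and feasibility, and the planned comparison with institutional data concerns safety outcomes. LPFS and DMFS carry no hypothesis, threshold or power, and PFS with death and OS are reported beside them. This objection stands in full.
- **Published series may define these endpoints differently.** Whether the results could be compared with other series depends on definitions that the article does not show, so nothing is claimed about that.
- **A competing-risk analysis is often left to the analysis plan.** Agreed. It is needed only if time to failure is the intended quantity.

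**Conclusion.** The point holds as a wrong stated rule for two secondary endpoints. Followed as written, the definitions and the Kaplan–Meier plan do not give the quantities named in the Objectives. Against a survival endpoint the medians come out too long; against a cumulative failure risk the curve reads too high.

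The direction does not depend on the assumed hazards. The size does: under the assumptions of Illustration 1, the LPFS median is about 34–63 months as written against 14–23 months with death counted, and one minus Kaplan–Meier at 5 years is 48–71% against 30–40%. These figures illustrate the effect and do not predict this trial's results.

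The consequence is confined to the reading of descriptive results in about 20 patients. The primary safety endpoint, the stopping rule and the sample size do not change. The definitions should be corrected before analysis.

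**What to change.** Amend the two definitions in Study endpoints. Let the LPFS event be locoregional failure or death from any cause, and the DMFS event be distant progression or death from any cause. Censor at the last negative imaging only patients who are alive without the event. The Kaplan–Meier plan then fits both names.

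If time to local or distant failure is what is wanted, rename the endpoints accordingly and report cumulative incidence with death as a competing event (Aalen–Johansen) in place of the Kaplan–Meier medians.

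The cost of the first option is two sentences. Deaths are already recorded for OS and the scans are already scheduled, so no new data are needed. The downside is that the reported medians become shorter.

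### Overall survival is censored at the last clinic visit while death carries no such limit, so the Kaplan-Meier estimate can be biased in a direction that depends on how deaths are learned of (low severity)

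*Protocol article*

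**What the plan says.** Under Study endpoints, the article fixes both the event and the censoring date for overall survival (OS): "Overall survival will be recorded as the time from IORT to death or last known clinic follow-up". Under Objectives, the purpose is to "Estimate median overall survival (OS) from time of IORT". The method is given under Statistical analysis and sample size: "Time to event outcomes such as OS, LPFS, DMFS, and PFS will be analyzed using Kaplan–Meier method".

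The Follow-up section sets the visits to which the censoring date is tied. The early schedule reads: "Patients will follow-up in clinic every 3 months with imaging for the first 2 years post-surgery". The spacing later doubles: "then every 6 months with imaging for years 3–5 post-surgery".

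On numbers and timing, Statistical analysis and sample size states that "25 patients will be enrolled with the expectation that 20/25 patients will undergo surgical exploration and IORT" and that "Data analysis will occur once the study has been completed". It does not define completion. The article does not say by what route deaths become known.

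**The concern.** Kaplan-Meier estimation needs the end of observation to be unrelated to the outcome. Here the two ways of leaving the risk set follow different clocks. A survivor is credited only up to a visit. A death carries no such limit, and it will usually fall between visits rather than at one.

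Take a patient seen at month 24 whose next visit is due at month 30, with a data cut-off at month 29. If the patient dies at month 27 and the study learns of it, the record is an event at 27 months. If the patient is alive at month 29 and the study knows it, the record is still censored at 24 months. Between months 24 and 27 this patient is in the risk set only if he or she dies, so the estimated hazard there is too high. The gap grows for anyone who stops attending clinic but whose death would still be reported.

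The opposite failure is also possible. If patients who leave clinic die without the study learning of it, they are censored as survivors and OS is overstated.

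The rule suits endpoints found on imaging: the same section ends local progression-free and distant metastasis-free survival at the last negative scan, because a scan is what detects those events. Vital status does not need a visit. At stake is the accuracy of a named secondary objective, the median OS.

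**Working it through.** The article gives no OS median, rate or event count, so there is no figure of its own to reproduce. The check is a simulation on the protocol's visit schedule.

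**Inputs from the article.** Visits at months 3, 6, ..., 24, then 30, 36, ..., 60 (Follow-up). Kaplan-Meier method and about 20 treated patients (Statistical analysis and sample size).

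**Assumptions not in the article.** Exponential survival with true median M of 18, 24 or 36 months. Uniform accrual over 24 months. Data cut-off 3, 12, 24 or 60 months after the last IORT, with follow-up capped at 60 months. Loss from clinic at 0, 1% or 3% per month. There were 200,000 simulated patients per scenario, so that bias is separated from sampling error.

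**Formulas.** True survival is S(t) = 0.5^(t/M). For M = 24, S(24) = 0.5^(24/24) = 0.50. With T the death time, C the cut-off and L the time of leaving clinic:
- Reference rule: event at T if T ≤ C, otherwise censored at C.
- Rule as worded, with all deaths captured: event at T if T ≤ C, otherwise censored at the last scheduled visit at or before min(C, L).

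**Step 1: reference rule.** With M = 24 it returns 24-month OS 0.50 and median 24.0 months, so the method is sound when deaths and survivors share one cut-off.

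**Step 2: rule as worded, all deaths captured, M = 24.**

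| Cut-off after last IORT | No loss: 24-month OS | No loss: median (months) | 3%/month loss: 24-month OS | 3%/month loss: median (months) |
|---|---|---|---|---|
| 3 months | 0.45 | 21.5 | 0.31 | 17.1 |
| 12 months | 0.48 | 22.8 | 0.38 | 18.8 |
| 24 months | 0.50 | 24.1 | 0.42 | 20.2 |
| 60 months | 0.50 | 24.0 | 0.47 | 22.0 |

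With 3% per month lost, the median shifts by 17.1 − 24.0 = −6.9 months at the earliest cut-off and 22.0 − 24.0 = −2.0 months at the latest. With no loss, the largest shift is 21.5 − 24.0 = −2.5 months, and it vanishes at the later cut-offs. A fresh simulation gave the same pattern (medians 17.3 to 22.0 with 3% loss and 21.4 to 24.1 with none).

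Medians of 18 and 36 months show the same direction. With M = 36 and no loss, a cut-off 24 months after the last IORT still gives 33.8 months; only the 60-month cut-off brings the bias to zero (36.1).

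**Step 3: the reverse case.** Cut-off 12 months after the last IORT, M = 24, with 10%, 20% or 30% of patients having a death that is never learned of, so that they are censored at the last visit before it. The 24-month OS becomes 0.52, 0.56 or 0.60 against a true 0.50. The bias is now upward.

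**Step 4: scale.** With 20 patients the standard deviation of the 24-month Kaplan-Meier estimate is about 0.11 to 0.18. Visit spacing alone shifts it by 0 to about −0.05. The 3% loss scenarios shift it by 0.50 − 0.47 = 0.03 up to 0.50 − 0.31 = 0.19, which at early cut-offs is as large as the sampling error. A confidence interval reflects sampling error but not this bias.

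**The case against.** The strongest objection is that only half of the asymmetry is written down. The censoring date is stated, but the article does not say that deaths are counted from any source. A reader might infer that from the unrestricted word for death, and might conclude that OS is certainly biased downward. The text does not support that certainty: with ascertainment unstated, unseen deaths would push the estimate up, as step 3 shows. This part of the objection stands, and the direction must remain conditional.

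A second objection is that the larger shifts rest on assumed drop-out, accrual and cut-off. That also stands. What the article does state points towards less bias: clinic visits run to year 5, patients who cannot keep to the follow-up schedule are excluded, and analysis waits for study completion. However, the exclusion acts at entry and cannot prevent a patient from moving to care elsewhere later. With 3% monthly loss some bias remains even after five years.

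A third objection is that cut-off dates and vital-status procedures commonly sit in the full protocol or analysis plan. Their absence from the article is indeed no finding. But the censoring date is a written rule, and an analysis plan that follows it inherits the problem.

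A reader might also infer that a distorted median OS would mislead the decision on a phase II trial. The Background and Discussion tie that step to safety and feasibility, and the planned comparison with institutional data concerns safety outcomes. That inference is not supported.

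**Conclusion.** The point holds in conditional form. The stated rule censors survivors at a clinic visit while death is unrestricted. This biases Kaplan-Meier OS downward if deaths are learned of outside clinic, and upward if deaths after the last visit are missed.

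On an assumed 24-month median, the downward shift is near zero with long follow-up and full attendance, and about 2 to 7 months if 3% per month leave clinic with every death still captured. These sizes rest on exponential survival, 24-month accrual and the listed cut-offs, none of which the article gives. They show a range and do not predict this trial.

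Severity is low: OS is estimated descriptively in about 20 patients, with no test, threshold or decision rule. The rule is still worth changing, because a better one is available at almost no cost.

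**What to change.** Replace the OS definition under Study endpoints with wording such as: OS is the time from IORT to death from any cause; vital status is checked in the same way for every treated patient at one data cut-off; patients not known to have died by then are censored at the date last known alive, from any source, up to that cut-off.

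The equal check must be part of the rule. Changing only the censoring date to last known alive would leave the asymmetry in place if deaths came from records or a registry while survivors were dated by their most recent contact.

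The cost is a short change of text and one vital-status check for about 20 patients. Treatment, visit schedule and sample size are unaffected.
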